#### Appropriate antithrombotic treatment according to stroke risk incorporating quality-control criteria

In those patients receiving anticoagulation with warfarin, we will only consider anticoagulation to be appropriate for this outcome if GPs, when reporting the six most recent INR results, report an INR result at least monthly and where at least four of the six test results (or two-thirds of results in cases where fewer than six are reported) are within therapeutic range (*i.e.*, within 2.0–3.0). These criteria for appropriate anticoagulation are based on local guidelines [44] and a consistently achieved standard of ‘time in therapeutic range’ reported in clinical trials [4-6], including one trial of general practice patients with an average age of 81 years [6].

#### Further refinement of outcome definition

Combinations of antiplatelet therapies with or without anticoagulation may diverge from standard guideline recommendations but may nonetheless be appropriate in the context of aspirin intolerance, patients with a history of coronary stenting, or in those affected by acute coronary syndromes [42,43,53-55]. We will accept other antiplatelet treatments, such as clopidogrel, dypridamole, and combinations of these treatments, where aspirin would have been considered the evidence-based treatment. Where anticoagulation is considered the evidence-based choice, we will not distinguish between cases where anticoagulation is used alone or in combination with other antithrombotics.

#### Decisional conflict

Scores comprising the seven-item decisional conflict scale, based on a previously validated measure [50] adapted for use in our earlier work and in other studies [13,14], will be summed to produce a total score, whereby higher scores indicate higher levels of decisional conflict (range = 7 to 35). At the time of writing, warfarin remains the only anticoagulant treatment that is available to all Australian residents via Australia’s universal health insurance scheme ensuring government subsidisation of medication. The fixed-dose anticoagulant dabigatran has received regulatory approval for AF but is not currently subsidised by the Australian government. Consequently, the uptake of dabigatran is not expected to be high, and we will restrict this outcome to items assessing decisional conflict about warfarin only, unless uptake of dabigatran is found to be common.

#### Sensitivity analyses

In cases that are lost to follow-up (for example, where GPs do not return their posttest audit questionnaires), we will reanalyse our primary and secondary outcomes relating to prescribing behaviour, firstly, assuming no change in antithrombotic management from baseline to posttest and secondly, assuming the desired outcome was not achieved.

#### Subgroup analyses

We will carry out subgroup analyses for our primary and secondary outcomes according to the following variables: (a) baseline CHADS_2_ scores (0, 1, or ≥2); (b) patient age (<65 years, 65–74 years, 75–84 years, ≥85 years); (c) baseline anticoagulation use (yes versus no); (d) patient sex.

#### Pretest comparisons between groups

We will compare groups on the numbers of patients selected by GPs, patient sex, age (mean and median differences and on categorical groupings <65 years, 65–74, 75–84, ≥85 years), CHADS_2_ scores (0, 1, ≥2, and mean scores), and use of oral anticoagulation (current at pretest, previous use, or never used).

#### Sample size estimate

Our study was powered to detect a 15% difference in anticoagulation rates between groups. We assumed a baseline use of anticoagulation of 50% to produce anticonservative (*i.e.*, larger) estimates of the required sample size. In the absence of a design effect, whereby the sample size would be adjusted for clustering of patients by GP, we required GPs to identify 170 patients per group or 340 in total [56]. As patient cases were clustered by GP, we adjusted our sample size estimate by the design effect *D*_eff_ = 1 + (*m* − 1)ρ [57], where *m* equals the average cluster size and ρ equals the intraclass correlation coefficient. We have selected a value of *m* to produce anticonservative (*i.e.*, larger) estimates of the required GP sample, as the number of GPs needed will have a greater effect on study resources and its feasibility than the numbers of patient cases identified by GPs. Smaller values of *m* will produce a sample size estimate requiring greater numbers of GPs. Assuming an average cluster size of three and selecting an intraclass correlation coefficient of 0.029, informed by results from a previous study [27], our anticipated design effect was 1.06 (*i.e.*, 1 + (3 – 1) × 0.029), producing a required total sample size of 1.06 × 340 = 361. Assuming 20% of posttest audit questionnaires are not returned by GPs, we require data on 452 de-identified patient cases or 226 per group. If GPs each select three patient cases on average, then we will need to recruit 76 GPs per group (*i.e.*, 226/3), or 152 in total.

#### Statistical analysis

Outcomes will be analysed according to the intention-to-treat principle, whereby patients are analysed according to the arm to which their GP cluster was allocated. Clustering will be accounted for at the practice level [57]. A *p* value of < .05 will be used to determine statistical significance of results. Analyses will be carried out by a statistician blinded to group allocation.

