**Methods:**

The STOP STROKE in AF study is a national, cluster randomised controlled trial designed to improve the uptake of anticoagulation in primary care. General practitioners from around Australia enrolling in this ‘distance education’ program are mailed written educational materials, followed by an academic detailing session delivered via telephone by a medical peer, during which participants discuss patient de-identified cases. General practitioners are then randomised to receive written specialist feedback about the patient de-identified cases either before or after completing a three-month posttest audit. Specialist feedback is designed to provide participants with support and confidence to prescribe anticoagulation. The primary outcome is the proportion of patients with atrial fibrillation receiving oral anticoagulation at the time of the posttest audit.

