### Randomisation

A statistician external to the study group is carrying out randomisation after participants complete academic-detailing sessions. Randomisation is being stratified by the number of cases GPs identify (≤2 or >3). Results of randomisation are communicated to the study coordinator (MG) who assigns GPs to their respective groups. The statistician involved in the analysis of the trial will receive the randomisation schedule directly from the statistician carrying out randomisation. Block randomisation is being used to control for date of entry into the trial. Block size will be disclosed to the study team only during the write-up of results.

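### The analysis sets the clustering level at the practice although the GP is the randomised unit; depending on the model, the primary standard error can be somewhat too small

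*Protocol article*

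**What the plan says.** The abstract describes the allocation: "General practitioners are then randomised to receive written specialist feedback about the patient de-identified cases either before or after completing a three-month posttest audit". The Randomisation section stratifies on a property of the GP and does not mention practices: "Randomisation is being stratified by the number of cases GPs identify".

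The Sample size estimate section takes the GP as the cluster: "As patient cases were clustered by GP, we adjusted our sample size estimate by the design effect". Its inputs are given per GP: "Assuming an average cluster size of three and selecting an intraclass correlation coefficient of 0.029". The target is 76 GPs per group.

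The Statistical analysis section then uses two different units in consecutive sentences. Intention to treat means that "patients are analysed according to the arm to which their GP cluster was allocated". The next sentence reads "Clustering will be accounted for at the practice level [57".

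**The concern.** The error term for a treatment comparison has to carry the variance of the unit that was randomised, which here is the GP. The practice is a different unit: under Pretest data collection, GPs report how many doctors work in their practice, so a practice can hold several. The article does not limit enrolment to one GP per practice, and it does not keep colleagues in the same arm.

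Suppose two colleagues are allocated to opposite arms and the model has a practice effect only. The model treats their difference as a within-cluster contrast. It removes shared practice variance from that contrast and adds nothing for variation between GPs. Yet the GP selects the cases, receives the feedback and reports the outcome, so correlation between patients should be expected at that level. The model-based standard error of the primary comparison is then too small, and the analysis does not match the design effect used for the sample size.

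**Working it through.** **1. The plan's own figure, with the GP as cluster.** Inputs from Sample size estimate: "We assumed a baseline use of anticoagulation of 50" percent, and "Our study was powered to detect a 15% difference in anticoagulation rates between groups", so 50% v 65%. Power and sidedness are not stated; 80% power and two-sided 5% are assumed because they reproduce the result.

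- n per group = [1.96·√(2·0.575·0.425) + 0.8416·√(0.25 + 0.2275)]² / 0.15² = 169.3, rounded up to 170 (340 in total).
- Design effect = 1 + (3 − 1)·0.029 = 1.058, used as 1.06. Then 1.06·340 = 360.4, giving 361.
- 361/0.8 = 451.25, giving 452, or 226 per group. 226/3 = 75.3, giving 76 GPs per group and 152 in total.

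The whole chain reproduces with the GP as cluster.

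**2. What a practice-only model does.** Take the largest case: every GP shares a practice with one other participating GP. Let m be patients per GP, ρ the GP-level ICC, and assume no extra correlation between colleagues. Total variance is scaled to 1 (a continuous analogue of the binary outcome).

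- The practice-only exchangeable correlation settles at the average over all pairs of patients in a practice: r = ρ(m − 1)/(2m − 1).
- Colleagues in opposite arms: the true variance of their difference is 2·DE/m, with DE = 1 + (m − 1)ρ. The model gives 2(1 − r)/m. Ratio q = (1 − r)/DE.
- Colleagues in the same arm: the model gives (1 + (2m − 1)r)/(2m) = DE/(2m), which is correct.
- Under individual randomisation about half the pairs are split. Weighting the two kinds of pair as the model would, model variance / true variance = q(1 + q)/(1 + q²).
- Type I error = 2[1 − Φ(1.96·√ratio)].

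m = 3 and ρ = 0.029 are the planned values. m = 5 is the minimum advised for second-phase GPs (Academic detailing). ρ = 0.10 is an assumption, not a figure from the article.

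| m | ρ | DE | r | q | model SE / true SE | type I error |
|---|---|---|---|---|---|---|
| 3 | 0.029 | 1.058 | 0.0116 | 0.934 | 0.982 | 5.4% |
| 5 | 0.029 | 1.116 | 0.0129 | 0.885 | 0.967 | 5.8% |
| 3 | 0.10 | 1.20 | 0.040 | 0.800 | 0.937 | 6.6% |
| 5 | 0.10 | 1.40 | 0.0444 | 0.683 | 0.885 | 8.3% |

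**3. Simulation under random allocation** (4,000 null trials per setting, Monte Carlo error about 0.35 points). With 122 GPs (about 80% of 152), 3 patients each and full sharing, practice-only v GP-level type I error was 6.0% v 5.5% at ICC 0.029, 7.0% v 5.6% at 0.10 and 9.6% v 6.0% at 0.20. With 152 GPs and full sharing, the practice-only model gave 5.4% (m = 3) and 5.7% (m = 5) at ICC 0.029, and 5.9% and 7.8% at 0.10. These agree with the table within simulation error.

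**4. Partial sharing.** With 10% of GPs in shared practices at ICC 0.029, practice-only and GP-level models gave 4.7% v 4.7% (122 GPs, m = 3), 4.9% v 4.8% (152 GPs, m = 3) and 5.2% v 5.1% (152 GPs, m = 5). With no sharing the two models are identical.

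**5. Robust standard errors.** Clustering by practice with a robust variance gave 4.7% to 6.1% across all scenarios, never more than 0.3 points from the robust variance by GP.

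**The case against.** The strongest case on the other side has four parts.

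*The estimator is not named.* The article says only at which level clustering is handled, and the model may properly be left to an analysis plan. GPs are nested in practices, so a robust variance by practice also covers correlation within GP. This stands. It rules out saying that a practice-level analysis understates the standard error wherever a practice has GPs in both arms; that holds only for a model-based practice-only error.

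*Sharing is probably rare.* GP recruitment drew individuals at random from a national database, not practices. The number of practices is not given. Assuming 3,000 to 8,000 equal-sized practices, 152 GPs form 152·151/2 = 11,476 possible pairs, so about 11,476/8,000 = 1.4 to 11,476/3,000 = 3.8 pairs of colleagues, or roughly 2% to 5% of GPs, with about half of those pairs split between arms. Self-selection could raise this. The point stands as a limit on size.

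*A much larger error might be inferred.* Placing one GP of every practice in each arm gives a simulated type I error of 8.4% at ICC 0.10 with 3 patients per GP, and 11.0% with 5. A reader might take 11% as the exposure. The documents do not support that: the Randomisation section describes blocked allocation of GPs with no pairing by practice, and the planned ICC is 0.029.

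*It may be a slip of wording.* The same reference is cited for the GP-based design effect and for the practice-level sentence, so one cluster may have been meant. That is possible but cannot be shown, and the article uses practice elsewhere for a unit with several doctors. If it is a slip, the sentence still needs correcting.

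**Conclusion.** The concern holds as an inconsistency in a rule that the article fixes for the primary comparison. The stated level is not the level of randomisation, and nothing in the article makes the two coincide. An analysis plan that followed the sentence literally could leave out GP-level variance.

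The likely consequence is small. At the planned ICC the standard error would be about 2% to 3% too small by the closed form (about 4% in the 122-GP simulation) even with full sharing, for a type I error of about 5% to 6%; with about 10% sharing the change is within simulation noise. Type I error of about 7% to 9% at an assumed ICC of 0.10 requires full sharing, and nearly 10% requires full sharing with an assumed ICC of 0.20. The extent of sharing and every ICC above 0.029 are assumptions. All of this applies only to a model-based practice-only standard error.

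Severity is minor to moderate. The documents do not show that the primary result would be invalid.

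**What to change.** Replace the practice-level sentence with: *The analysis will account for clustering of patients within GP, the unit of randomisation; where a practice contributes more than one GP, practice may be added as a further level.* If practice was meant as another word for the individual GP, say so.

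This costs one sentence. It needs no extra patients and leaves the sample size at 452 cases and 152 GPs, which already rests on GP clusters. The Progress section expects posttest data collection to finish in 2012 and results in 2013, so the change can be made before the blinded analysis. Reporting how many practices contributed more than one GP would show readers whether the choice mattered.

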#### Ethics approval

The Human Research Ethics Committee of the University of New South Wales has approved the study (UNSW HREC Reference Number 07067).

## Discussion

Long-term anticoagulation for AF remains the treatment of choice to prevent stroke in most people with AF. The STOP STROKE in AF study has an active ‘control’. Information is delivered via academic detailing with tailored feedback about risk stratification and guideline recommendations. The addition of expert decisional support in our intervention arms allows for a direct test of this component on GP self-reported patient management. The national geographical reach of the study and feasible delivery of the intervention, via telephone and mail, are innovations of the study.

Until recently, warfarin has been the only oral anticoagulant available for managing AF. Two fixed-dose anticoagulants, dabigatran [46,47] and rivoroxaban [58], have received approval for stroke prophylaxis in AF by the US Federal Drug Administration (FDA). Apixaban [59], another fixed-dose anticoagulant, is due to be reviewed by the FDA in 2012. It is unclear whether the advent of new drugs will improve anticoagulation rates. In practice, uptake of dabigatran, the first FDA-approved fixed dose oral anticoagulant, has been described as ‘disappointing’, with an estimated 10% of AF patients using the drug in the United States [60]. The cost of the drug, the need for twice-daily dosing, a short shelf-life, the lack of an antidote to reverse acute bleeding, the inability to determine the anticoagulation effects of dabigatran, and the increased risk of GI bleeding, dyspepsia, discontinuation, and possibly myocardial infarction, when compared with warfarin, may limit its broader uptake [58]. Recent warnings from regulators in Australia [48] and the United States [61] have emphasised safety concerns about dabigatran, particularly in those with renal impairment and in elderly patients aged over 75 years. In Australia, AF became an approved indication for dabigatran by the local government regulator, the TGA, after which the company manufacturing the drug offered doctors free medication for a limited period of time, or until the drug became subsidised by the Australian government (whichever occurred first). The Australian government has thus far declined the company’s application to subsidise the drug. Federal agencies in Australia are currently undertaking a further review of the costs and benefits of the new drug and defining the circumstances in which warfarin may be more cost effective. Other fixed-dose anticoagulants that may come to market in the near future, specifically rivaroxaban and apixaban, share some drawbacks of dabigatran; all three lack an antidote to reverse acute bleeding, and apixaban also requires twice-daily dosing.

Prescribing behaviour seems difficult to shift. The South London secondary prevention programme, also called Stop Stroke, enrolled 523 stroke survivors, 99 of whom had AF. Patients were randomised to receive ‘keeping well plans’ summarising risk factors and management strategies, including evidence-based prescribing for managing blood pressure, diabetes, and AF, that were updated over a 12-month period [33]. The intervention had no effect on any of the study outcomes, including anticoagulant prescribing for AF patients.

Clinician fears about the side effects of anticoagulation appear to have greater influence on anticoagulant prescribing than do concerns about stroke risk. Clinicians are less likely to prescribe anticoagulation in patients with AF if one of their AF patients receiving anticoagulation is hospitalised for a major bleed, yet prescribing behaviour is not influenced if untreated AF patients are hospitalised for an ischaemic stroke [62]. In our national Australian survey [13,14], GPs with prior experiences of a haemorrhagic stroke in AF patients report a heightened sense of responsibility for that outcome. In contrast, GPs with untreated AF patients who had a stroke were no more likely to feel responsible for this outcome than other GPs. Further, our survey showed that GPs appeared overly cautious in prescribing anticoagulation in the presence of any perceived risk of bleeding, even where treatment benefits clearly outweighed the risk of harm. Other Australian surveys show that GPs are reluctant to prescribe anticoagulation for nonvalvular atrial fibrillation in the elderly or in the presence of perceived bleeding risks, which would not contraindicate anticoagulation according to available evidence [15-17].

The STOP STROKE in AF study aims to redress clinician wariness and concerns over the use of anticoagulation and support effective decision making to build practitioner confidence and increase the appropriate uptake of anticoagulation in AF.

In addition to our own research, we are aware of one other Australian study evaluating a risk assessment tool in general practice for improving the management of AF [63,64]. It is hoped that these studies will collectively identify effective implementation strategies to better inform GPs on AF management, closing the evidence–practice gap in Australia and elsewhere.

### Progress

Required numbers of GPs have been recruited. We expect posttest data collection to be completed in 2012. Results are expected in 2013.
